### Participant timeline

•For physiotherapy (five days weekly for one month)•
*Karma Basti* (alternate regime of
*Niruha Basti* with
*Dashmoola Kwatha* and
*Anuvasana Basti* with
*Dashamoola* oil for complete one month, i.e., Day 1
^st^–Day 30
^th^)

Time schedule of enrolment: Patients with the first Stroke diagnosed with CT/MRI (thrombolytic Stroke only) without other neurological deficits but <6 months of onset will be enrolled for the study.

Interventions (including any run-ins and washouts): There are no washout periods; the intervention of Panchakarma treatment and Physiotherapy sitting for 30 days.

Assessments and visits for participants: Assessment will be carried out at baseline level and after the intervention, i.e., on the 30
^th^ day, then follow-up visits on the 60
^th^ and 90
^th^ day.

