### Interventions

For group A, standard control modern treatment (Anti-thrombotic treatment, e.g. Tab. Ecosprin 75/150 mg OD and Tab. Notropril 800 mg TDS) will be given along with physiotherapy. The physiotherapy sitting for motor relearning program and functional stimulation will be given for 55 mins per sitting, five days weekly for one month.

For group B, standard control modern treatment will be given along with Ayurveda Panchakarma and physiotherapy. In this case, gentle massage with
*Dashmoola Taila* +
*Nadi Sweda* with
*Dashmoola Kwatha* + medicated enema (alternate regime of
*Dashamoola Niruha Basti* with
*Anuvasana Basti* with
*Dashmoola Taila* will be prescribed for the treatment. The alternative regime of medicated enema i.e.,
*Anuvasana Basti* (oil enema) and
*Dashamoola Niruha Basti* (decoction enema) will be given on odd and even days respectively for one month, and physiotherapy for five days weekly for one month.

The study’s methodology is mentioned in
Table 1 and the flowchart of the study design or methodology is given in
Figure 1.

**Table 1. T1:** Methodology of the study.

Group	Sample size	Intervention	Type of Treatment	Duration of treatment	Total duration	Follow-up
**A**	20	Standard Control	Modern + Physiotherapy (MRP+FES)	For Physiotherapy sitting (55 mins/sitting)	Physiotherapy (Five days weekly for one month)	on 60 ^th^ & 90 ^th^ Day
**B**	20	Standard Control + *Panchakarma*	Modern + Physiotherapy (MRP+FES) Gentle massage with *Dashmoola Taila* + *Nadi Sweda* with *Dashmoola Kwatha* + Medicated Enema (Alternate regime of *Dashamoola Niruha Basti* with *Anuvasana Basti* with *Dashmoola Taila*	• Same as group A+ *Dashmoola Basti* Details of *Dashmoola Basti* Are as follows: • Local *Snehana*-10 mins • Local *Swedana*-10 mins or till attainment of *Samyak Swinna Lakshana*, whichever is earlier.	• Panchakarma for complete one month (Day 1 ^st^ – Day 30 ^th^) • Physiotherapy for Five days weekly for one month	on 60 ^th^ & 90 ^th^ Day

* FES – Function Electrical Stimulation, MRP – Motor Relearning Programme.

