*Anuvasana Basti Lakshana*).
^
21
^ Moreover, it also increases the therapeutic outcome of these therapies by improving blood circulation in that local region.

As local massage nourishes the muscular tissue and fomentation with
*Dashmool* decoction, massage instantaneously relieves the extremities’ stiffness, especially muscular tissues. Both these procedures also play an important role in enhancing the speed of rehabilitation of the stroke, resulting in a speedy recovery in cognitive functions hampered in it. According to Ayurveda, vitiation of
*Vata* is the most important factor responsible for inducing impairment of cognitive functions and musculoskeletal movements.
^
22
^ Both procedures used
*Dashmoola* oil and
*Dashmoola* decoction, respectively, to pacify vitiated
*Vata* due to their
*Snigdha* &
*Ushna Guna*. Moreover, both improve the patient’s gait and reduce the dependency of the affected individual on relatives.
^
23
^
^,^
^
24
^ Local massage and fomentation with
*Vata* pacifying medicines improve the patient’s quality of life by building confidence and contributing to inducing expected positive outcomes.
^
25
^

On the other hand, the efficacy of physiotherapy, especially of the “Motor Relearning Program” (MRP) and “Functional Electrical Stimulation” (FES) in the early rehabilitation of the stroke can be justified as follows:

Motor learning theory underpins the Motor Relearning Programme (MRP). Carr and Shepherd claimed that motor control training necessitates anticipatory acts as well as continuing exercise. The motor relearning program is useful for improving a group of post-stroke patients’ balance function and functional performance. It consists of four distinct steps, i.e., to analyze the task and practice the missing component and task with a transference of training. Eight studies suggested that MRP planned for five weeks showed better improvement in functional performance on self-care, instrumental activities of daily living, and integration into the community hospital.
^
26
^

The FES is based on electrical stimulation to the peripheral nerves that innervate the paralyzed muscle to generate action potentials in motor neurons, propagating towards the power and causing its contraction. According to John E.R. 1999
*et al.* and Niu
*et al.*, 2019, it is an excellent recovery tool for motor functions hampered in post-stroke conditions.

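### The Day-30 assessment falls on the last day of massage, sudation and enema given to Group B only, so its stiffness comparison can mix a same-day effect with lasting recovery

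*Protocol article*

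**What the plan says.** Under Participant timeline, the post-treatment visit is fixed as follows: "Assessment will be carried out at baseline level and after the intervention". The article dates this visit to Day 30, and the same sentence adds follow-up visits on Days 60 and 90. The line before it reads: "There are no washout periods; the intervention of Panchakarma treatment and Physiotherapy sitting for 30 days".

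Table 1 (Interventions) gives the Group B course as "Panchakarma for complete one month (Day 1"; the entry ends at Day 30. Its components are set out in the text beginning "For group B, standard control modern treatment will be given along with Ayurveda Panchakarma and physiotherapy. In this case, gentle massage with": oil massage, steam sudation, and oil and decoction enemas on alternate days. Group A has no counterpart to these. Its medication "will be given along with physiotherapy. The physiotherapy sitting for motor relearning program and functional stimulation will be given for 55 mins per sitting". The physiotherapy schedule, on five days of each week, is the same in both groups.

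The Discussion, explaining why massage and fomentation are included, says: "decoction, massage instantaneously relieves the extremities’ stiffness, especially muscular tissues".

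Resistance to passive movement on the Modified Ashworth scale appears among the primary outcomes under Variables to be measured, and among the secondary goals in the Introduction. The analysis paragraph specifies paired and unpaired t-tests without naming a time point.

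**The concern.** The trial asks whether the Ayurvedic package improves rehabilitation after stroke. A measurement taken on a treatment day can pick up two things: change that has built up over the month, and relief from the session just given. If the second occurs in one arm only, the between-group difference contains it. Here the protocol's own rationale asserts such immediate relief, and asserts it for stiffness, which one of its outcomes measures directly.

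At stake is the meaning of a Day-30 difference in Modified Ashworth score. It could be reported as recovery when some or all of it would be gone soon after treatment stops. The analysis could not correct this afterwards if the interval since the last session is neither standardised nor recorded.

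**Working it through.** **Step 1: set treatment days against assessment days.** The last scheduled Panchakarma day is Day 30 (Table 1 and Participant timeline).

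| Assessment | Days since last Group B session |
|---|---|
| Day 30, after that day's session | 30 − 30 = 0 |
| Day 30, before that day's session | 30 − 29 = 1 calendar day |
| Day 60 | 60 − 30 = 30 |
| Day 90 | 90 − 30 = 60 |

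The wording does not say outright which of the first two rows applies. Placing the assessment after the intervention suggests the first, and nothing requires the second.

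**Step 2: which arm is exposed.** Massage, sudation and enema are scheduled for all 20 Group B patients and for none of the 20 in Group A. Physiotherapy follows the same five-day schedule in both arms and creates no imbalance.

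**Step 3: which outcomes are exposed.** The protocol claims immediacy for stiffness of the extremities only, and attributes it to massage, in a sentence that also mentions fomentation. The outcome that measures this is the Modified Ashworth scale. Nothing similar is said of the enema, or of the Fugl-Meyer, balance, gait, Barthel, quality-of-life or NIHSS measures.

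**Step 4: what the Day-30 contrast estimates.** Let L be the lasting group difference and T the same-day effect in Group B. The expected Day-30 difference is L + T, so the bias for L is T at any sample size. By Day 60, T should have faded. A fall from Day 30 to Day 60 equals T plus any real loss of L, and the planned data cannot separate the two.

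**Step 5: illustrate the size.** The protocol gives no magnitude for T and no standard deviation, and its 20 per group is set on practical grounds, so there is no stated power figure to reproduce. Assume L = 0, T = d standard deviations, n = 20 per group, and an unpaired t-test at two-sided 0.05 (the 0.05 is also an assumption). Degrees of freedom are 2 × 20 − 2 = 38, and the noncentrality is d × √(n/2) = d × √10.

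| Assumed d | Noncentrality | Chance of p < 0.05 at Day 30 |
|---|---|---|
| 0 | 0 | 5% |
| 0.2 | 0.63 | 9.5% |
| 0.3 | 0.95 | 15% |
| 0.5 | 1.58 | 34% |
| 0.8 | 2.53 | 69% |
| 1.0 | 3.16 | 87% |

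The Modified Ashworth scale is ordinal, so standard-deviation units are only a rough guide.

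**The case against.** The strongest reply is that the protocol already has off-treatment assessments. Days 60 and 90 come 30 and 60 days after the last session, and an end-of-treatment visit followed by two later ones is an ordinary design. This largely stands. A reader might infer that a transient effect is bound to be reported as rehabilitation benefit; the documents do not support that, because they do not make Day 30 primary. They do not make a later visit primary either, and the Introduction stresses recovery within a short time, so Day 30 could still become the headline.

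Second, the text can be read as placing the assessment after the month's course rather than after that day's session. A reader might infer that every Group B patient is tested within hours of massage and enema, but the article does not say so. The order of procedures within a visit could be set in the full protocol or the assessment proforma, which are not shown. What remains is that the article fixes the visit on a treatment day and states no interval.

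Third, a reader might infer that balance, gait and motor scores are equally affected. The protocol's claim covers stiffness only. Carry-over to the other tests is plausible, but its direction and size are unknown.

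Fourth, the Modified Ashworth scale has no percentage in the list of improvements that will count as significant, and the Introduction treats it as secondary. That lowers the stakes, but the scale is still listed among the primary outcomes elsewhere in the article.

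Finally, massage is part of the treatment, so its immediate effect is arguably part of the treatment effect. That would be a sound answer if the question were relief on a treatment day. The stated question is rehabilitation.

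**Conclusion.** The point holds in a limited form. The Day-30 visit coincides with the last day of a course given to one arm only, with no washout, and the protocol itself asserts an immediate effect on what one of its outcomes measures. The Day-30 difference on the Modified Ashworth scale can therefore mix a same-day effect with lasting recovery. For the other instruments this is a reasonable suspicion and no more.

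The overlap is certain; the size of the bias is not. The range of about 9.5% to 87% for a false Day-30 finding rests wholly on assumed transient effects of 0.2 to 1.0 SD and no lasting effect. The off-treatment visits contain the problem provided they are given due weight. This is a worthwhile, inexpensive improvement that has to be made before the Day-30 data are collected. It does not invalidate the trial.

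**What to change.** Keep the end-of-treatment visit and state its timing relative to treatment. Either carry out all its assessments before any trial session on Day 30, or hold the visit on Day 31-32. Use one rule for both arms. The later option gives the clearer gap: an assessment before the Day-30 session still follows the Day-29 session by about a day at most, depending on clock times.

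Add a field to the follow-up assessment proforma for the time since the last session. State that any Day-30 difference in stiffness will be read alongside the Day-60 and Day-90 results.

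The cost is a sentence or two in the protocol, one field on the form, and a shift of the visit by hours or by a day or two. No treatment changes, and no extra patients or procedures are needed.

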### Assignment of interventions (for controlled trials)

Patients will be recruited by simple randomization through the computer-generated table. The principal investigator (PI) and co-investigator (CO-I) will allocate and enroll the patient. Using computer-generated random numbers, the researcher creates random allocation cards. The researchers will keep the original randomly assigned sequences in a safe place and use a different copy to sign up the patients.

The envelopes will be marked with serial numbers on the outside. The date, time, patient ID, post-procedure results, and other required details will be on the envelope.

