**Methods:**

A total of 40 patients will be enrolled and divided randomly into two equal groups. In Group A (control), standard treatment (modern + physiotherapy) will be prescribed for one month. In Group B (interventional group),
*Dashmoola Basti* will be added to the aforementioned standard treatment for one month.

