### Study design

It is an interventional study, it is a superiority clinical trial, i.e., randomized reference standard control open-labeled two-arm comparative clinical trial.

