### Sample size

Due to practical considerations such as cost, patient inconvenience, judgments not to proceed with an investigation or a lengthy study duration, the number of participants in the study is restricted. So for the phase-I trial, 20 sample size is considered for each group.
^
3
^

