### Recruitment

Daily visit to the stroke inpatient ward is planned at Acharya Vinoba Bhave Rural Hospital, and if the patient is willing to enroll in the said study can be recruited for the study after written informed consent. Patients will be added one at a time until the target sample size is reached.

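### Simple randomisation does not guarantee the two equal groups of 20 that the protocol promises, and the enrolling investigators work from a copy of the sequence in an open-label trial

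*Protocol article*

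**What the plan says.** Three places fix the group sizes. The abstract (Methods) states: "A total of 40 patients will be enrolled and divided randomly into two equal groups". The Sample size section states: "So for the phase-I trial, 20 sample size is considered for each group". Table 1 prints 20 for group A and 20 for group B.

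The method is named under Assignment of interventions: "Patients will be recruited by simple randomization through the computer-generated table". That section goes on to allocation cards made from computer-generated random numbers and to serially numbered envelopes. It states no block, no fixed number of cards per arm, and no rule for when an arm is full.

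Four further statements bear on who can foresee an assignment:

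- Study design: a "randomized reference standard control open-labeled two-arm comparative clinical trial".
- Recruitment: "Patients will be added one at a time until the target sample size is reached".
- Assignment of interventions: "The principal investigator (PI) and co-investigator (CO-I) will allocate and enroll the patient".
- The same section: "The researchers will keep the original randomly assigned sequences in a safe place and use a different copy to sign up the patients".

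The Setting section adds that patients who withdraw are replaced. It does not say how a replacement is allocated.

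**The concern.** The promised group sizes are not a property of the named method. Under simple randomisation each patient is assigned independently, so the final split is a binomial outcome and usually not equal. To obtain 20 and 20, something must be added to the method, and the protocol does not say what.

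What is at stake is mainly concealment, not precision. Any device that forces balance makes some assignments foreseeable to a person who knows the running totals and the target. Here the target is stated, the trial is open label, and the people who decide whether to enrol the next patient also allocate. If they can foresee an assignment, they can steer who enters which arm, and the comparison is then open to selection bias that no analysis can reliably remove. The statement that the researchers use a copy of the sequence to sign up patients raises the same risk more directly, whatever the form of the list.

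**Working it through.** **Inputs.** N = 40 and 20 per arm (abstract, Sample size, Table 1). Method: simple randomisation (Assignment of interventions). Probability 0.5 per arm is an assumption; it follows from the intention to have equal groups. The 20 per group rests on practical grounds, with no power calculation, so there is no sample-size figure to reproduce.

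**1. Chance of the promised split.** The number in arm A is binomial(40, 0.5).

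- P(20/20) = C(40,20)/2^40 = 0.1254, so the arms are unequal in 87.5% of trials.
- P(22/18 or worse) = 63.6%.
- P(24/16 or worse) = 26.8%.
- P(26/14 or worse) = 8.1%.
- Mean absolute difference between arms = 5.0 patients.

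**2. Cost in precision.** For arms of a and b with a common variance, efficiency relative to 20/20 is 4ab/40².

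- 24/16: 4 × 24 × 16 / 1600 = 0.96.
- 26/14: 4 × 26 × 14 / 1600 = 0.91.
- On average: 4ab = 40² − (a − b)², and the expected value of (a − b)² is 40, so mean efficiency = 1 − 40/1600 = 0.975. This is a loss of 2.5%, worth about one patient in 40.

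**3. Determined allocations if balance is forced.** The protocol states neither of these rules; they show the range.

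- *Arm closed at 20.* If the other arm has t patients at closure, 20 − t assignments are forced. The mean is the sum over t = 0 to 19 of (20 − t) × 2 × C(19 + t, t)/2^(20 + t), which equals 40 × C(40,20)/2^40 = 5.01. A simulation of 200,000 trials gave 5.01. The median is 4, at least one is always forced, and ten or more are forced in about 10% of trials.
- *Shuffled list of 20 + 20.* The mean length of the determined tail is 40/21 = 1.90.

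**4. Guessability in an open-label trial.** Suppose an investigator always guesses the arm that is behind, and tosses a coin when the arms are level. For a balanced block of size n, the expected number correct is n/2 + 2^(n−1)/C(n, n/2) − 0.5.

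| Scheme | Correct of 40 | Arithmetic |
|---|---|---|
| Simple, no restriction | 20 | chance |
| Simple, arm closed at 20 | 22.5 | 20 + 5.01/2 |
| Shuffled 20 + 20 list | 23.5 | 20 + 2^39/C(40,20) − 0.5 = 20 + 3.99 − 0.5 |
| Random blocks of 2, 4 and 6 | 28.1 | gain over chance per block 0.5, 0.833 and 1.1; mean 0.811 per 4 patients; × 10 = 8.1 |

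Simulation of the last scheme, with the blocks constrained to total 40, also gave 28.1. Keeping the block sizes undisclosed does not help against this guess, because it uses only the running totals.

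**The case against.** The strongest reply is that this is loose wording. Allocation cards and numbered envelopes are compatible with a pre-made set of 20 + 20 shuffled cards. That would give exact balance, and the phrase simple randomisation might then mean only unblocked and unstratified. A planned number per arm is also often read as a target, no power calculation depends on exact equality, and the unpaired t-test is valid with unequal arms. Unrestricted simple randomisation is itself defensible in an unblinded trial, because no assignment can be guessed from earlier ones.

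Much of this stands. The precision loss is minor, and a 20 + 20 deck is possible. But the article states no such deck, and a deck of that kind is restricted randomisation, so the named method would still be wrong. The article's brevity does not explain the conflict: it names a method that does not fit its own group sizes.

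Two stronger readings are tempting, and the document supports neither. A reader might infer that simple randomisation cannot give equal groups; it can, in 12.5% of trials. A reader might also infer that about five late allocations will be predictable; that figure holds only if an arm is closed at 20, and no such rule appears.

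A third inference is that the investigators can see all 40 assignments in advance. The text says that a copy is used at sign-up. It does not say that the copy can be read ahead of the next patient, so this is a risk to be closed and not an established fact.

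**Conclusion.** The point holds as an inconsistency with a practical consequence. The stated sizes and the stated method do not go together: assuming probability 0.5 per arm, the promised 20/20 occurs in 12.5% of trials and a split of 24/16 or worse in 27%. The direct statistical cost is small, about 2.5% of precision on average.

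The number of fully determined assignments depends on how balance would be obtained, which is not stated: none if it is not forced, a mean of 1.9 with a shuffled 20 + 20 list, and a mean of 5.0 with an arm closed at 20. The replacement of withdrawn patients could add to this if replacements were used to restore a group to 20, which the document leaves open.

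The more serious exposure is the custody of the list. In an open-label trial the same investigators enrol, allocate and work from a copy of the sequence. If that copy is readable, foreknowledge is not limited to the last few patients, and the type of list no longer matters. The plan should be corrected before enrolment; the point is not fatal to the trial.

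**What to change.** Replace simple randomisation in the section on assignment of interventions with a pre-generated restricted 1:1 list that totals 20 + 20. Use either a random allocation rule (one shuffled list of 20 + 20) or large undisclosed blocks. Small blocks of 2, 4 and 6 are not advisable here because of their guessability.

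Have the list held by someone outside the enrolling team, who releases each assignment only after the patient has been enrolled. Remove the statement that the researchers sign up patients from a copy of the sequence. State how a replacement for a withdrawn patient is allocated.

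Alternatively, keep simple randomisation, describe 20 per group as an expected number, and drop the promise of equal groups in the abstract, the Sample size section and Table 1. The independent custody of the list is needed in this case too.

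The cost is one new list from the same software and one person outside the enrolling team to hold it. The downside of the restricted list is some guessability in an open-label trial: about 23.5 of 40 correct for a 20 + 20 list, against 20 by chance and 28.1 for random blocks of 2, 4 and 6. The downside of the alternative is the average precision loss of about 2.5% and an occasional marked imbalance.

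### The investigators who enrol patients are to sign them up from a copy of the random sequence, so allocation concealment is unprotected in an open-label trial

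*Protocol article*

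**What the plan says.** The section of the protocol article on assignment of interventions describes the procedure in six sentences.

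- Method: "Patients will be recruited by simple randomization through the computer-generated table".
- Who enrols and who allocates: "The principal investigator (PI) and co-investigator (CO-I) will allocate and enroll the patient".
- Who prepares the allocation: "Using computer-generated random numbers, the researcher creates random allocation cards".
- Custody and use of the sequence: "The researchers will keep the original randomly assigned sequences in a safe place and use a different copy to sign up the patients".
- Envelopes: "The envelopes will be marked with serial numbers on the outside".
- What is written on them: "The date, time, patient ID, post-procedure results, and other required details will be on the envelope".

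Three other statements bear on the point. The Study design section calls the trial a "randomized reference standard control open-labeled two-arm comparative clinical trial". The Recruitment section plans daily visits to the stroke ward, enrolment after written consent, and sequential entry: "Patients will be added one at a time until the target sample size is reached". The data and analysis section names paired and unpaired t-tests and no baseline covariate.

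**The concern.** Concealment means that whoever decides whether and when to enter a patient cannot know that patient's arm until the decision is final. The stated procedure does not secure this. The investigators who enrol also allocate, and sign-up runs from a copy of the sequence. Locking the original away guards against loss or alteration. It does not hide the next assignment from people working from the copy.

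The setting leaves room for such knowledge to matter. Staff visit the ward daily and add patients singly, so they can choose whom to approach and when. The eligibility criteria admit any onset under six months and ages 45 to 60, so eligible patients may differ in prognosis. The Setting section has withdrawn patients replaced, which creates further slots to fill. Because treatment is open, concealment before assignment is one of the few protections against bias that the trial can have. Selection at entry would affect the group comparison on every outcome and cannot be reliably repaired in the analysis.

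**Working it through.** **Step 1. The roles, side by side (all from the assignment section).**

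| Task | Person named |
|---|---|
| Create the allocation cards | the researcher |
| Keep the original sequence | the researchers |
| Sign patients up from a copy | the researchers |
| Enrol | principal investigator and co-investigator |
| Allocate | principal investigator and co-investigator |

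The last three rows are enough. Signing patients up is enrolment, enrolment belongs to the two investigators, and the tool used for it is a copy of the sequence. Who generated the list does not change this. No row names a person outside enrolment.

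**Step 2. Do the envelopes restore concealment?** An envelope conceals only from people who cannot learn its contents another way. If the enrolling team holds a list in the same serial order, the number on the outside identifies the arm inside. The copy and the envelopes are therefore two incompatible mechanisms unless the copy is itself the set of cards inside the envelopes, and the text does not say that it is.

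**Step 3. Is there a figure in the plan to reproduce?** No. The sample size of 20 per group is set on practical grounds, without a significance level, power, effect size or SD. The size of any bias cannot be derived from the documents.

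**Step 4. Illustration under assumed shifts.**

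Inputs: n = 20 per group (Sample size section); unpaired t-test (data and analysis section); two-sided 5% level (assumed, as the article states none); no treatment effect; selection shifts the group means by d SD, with d = 0.10 to 0.20 (assumed). One way to reach these shifts is for 20% to 40% of Group B places to go to patients with a prognosis 0.5 SD better: 0.20 × 0.5 = 0.10 and 0.40 × 0.5 = 0.20. Both the share and the 0.5 SD are assumptions.

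- Standard error of the difference: √(2/20) = 0.316 SD.
- Degrees of freedom: 20 + 20 − 2 = 38; two-sided 5% critical value 2.024.
- Noncentrality: d / 0.316 = 0.316 at d = 0.10 and 0.632 at d = 0.20.
- Rejection probability, both tails of the noncentral t:
  - d = 0.10: 0.0493 + 0.0117 = 0.061
  - d = 0.20: 0.0896 + 0.0050 = 0.095

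The nominal 5% error becomes about 6.1% to 9.5%. A larger assumed shift gives more: 12.0% at d = 0.25.

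**The case against.** The strongest reply is that non-concealment is inferred. The section mentions cards, an original kept safe, a copy and numbered envelopes. The copy could be the cards sealed inside the envelopes, and nothing says that a list is consulted before consent. A reader might go further than the text and conclude that all 40 assignments are certainly known in advance and that selection bias is built in. The documents do not support that. It assumes that the copy is an open list and that the investigators would act on it. What stands is that the plain wording has patients signed up from a copy of the sequence and that nothing in the section rules out the open-list reading. Consent before recruitment does not help, because the choice of whom to approach comes before consent.

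A reader might also infer that the principal investigator or co-investigator generates the sequence. That is a close reading and not what is written: the text says only the researcher. The point does not need it.

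A journal article condenses the full protocol, so missing words such as sealed or opaque carry no weight. I accept that and do not rely on them. The concern is with a procedure the article states.

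It would be too strong to say that t-tests correct nothing. A comparison of change from baseline would remove part of a difference in baseline level. It would not remove a difference in recovery potential, which is what an enroller could select on.

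Sequential entry is ordinary practice and is not evidence of foreknowledge. It only gives foreknowledge something to act on.

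Finally, writing post-procedure results on the envelope adds little exposure when treatment is open, and the term is not defined. It is a wording matter and not part of the main concern.

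**Conclusion.** The concern holds as an unprotected risk arising from a stated procedure. The same two investigators enrol and allocate, the sequence is copied for use at sign-up, nobody independent is named as its holder, and the envelope wording does not fit with the copy. The exposure rests on the text. The size of any bias does not: the 6.1% to 9.5% range depends entirely on assumed shifts of 0.10 to 0.20 SD and a two-sided 5% test, and its lower end is only about one percentage point above nominal. The case for acting therefore rests on the design principle, on the difficulty of repairing selection at entry afterwards, and on the low cost of the remedy. This should be corrected before patients are enrolled under the present wording.

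**What to change.** 1. Delete the use of a copy of the sequence at sign-up, and state that the enrolling investigators hold no copy.
2. Name, by role, an existing staff member with no part in enrolment, treatment or assessment, who generates and holds the only sequence and prepares sequentially numbered, opaque, sealed envelopes.
3. State that each envelope is opened in order, and only after eligibility, consent and baseline scores have been recorded.
4. As a minor wording change, record results on the case record form and not on the allocation envelope.

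The cost is a few sentences of protocol text and a short hand-over to a colleague, assuming one is available. It adds no patients, visits or procedures.
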